### Sample

One hundred and twenty preterm infants (60/group) will be enrolled. Infants are included if they are less ≤ 32 weeks PMA at birth and parents provide informed written consent. Infants are excluded if they have known gastrointestinal, craniofacial, cardiovascular, neuromuscular, and/or genetic defects. Infants of both genders and all ethnic and racial backgrounds are recruited. We expect approximately 5 % of the sample to be Hispanic and 50 % to be Black/African American. Approximately 10 % of the sample is expected to be multiple gestation (twin or triplet). Two to three infants are enrolled per month; this number is based on data from the clinical setting, our experiences in previous studies, the length of the intervention, and our data collection processes. Infants who are medically unable to transition to oral feeding by 40 weeks PMA are excluded from further study.

Infants are recruited by research nurses who are experienced in neonatal care and trained in study procedures. Initial contact is generally made within 24 to 48 hours after the infant’s birth. A study brochure is provided to parents and a demonstration of study procedures using a doll is given. Parents are encouraged to think about participation for as long as they need; study nurses usually contact parents within 1 to 2 days of first contact to obtain parents’ decision.

A randomization scheme was created by the study statistician for study group assignment using Statistical Analysis Software (SAS 9.3, SAS Institute Inc., Cary, NC, USA). The random group assignments are placed on a card and sealed, only to be used after an infant was enrolled. Once enrolled, infants are randomly assigned to either the intervention or the control group by drawing a card from the assignment set. Parents of twins are allowed to request a single randomization card for both twins or to allow their infants to be randomized independently. Only one twin from a twinset where both infants were randomized with the same card will be included in the analysis.

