**Methods:**

This trial uses an experimental, longitudinal, 2-group design with 120 preterm infants. Infants are enrolled within the first week of life and randomized to an experimental group receiving a patterned feeding experience from the first gavage feeding through discharge or to a control group receiving usual feeding care experience. The intervention involves a continuity of tactile experiences associated with feeding to train and build neuronal networks supportive of normal infant feeding experience. Primary outcomes are neurobehavioral organization as measured by Neurobehavioral Assessment of the Preterm Infant at 3 time points: the transition to oral feedings, NICU discharge, and 2 months corrected age. Secondary aims are cognitive function measured using the Bayley Scales of Infant and Toddler Development, Third Edition at 6 months corrected age, neurobehavioral development (sucking organization, feeding performance, and heart rate variability), and clinical outcomes (length of NICU stay and time to full oral feeding). The potential effects of demographic and biobehavioral factors (perinatal events and conditions of maternal or fetal/newborn origin and immunologic and genetic biomarkers) on the outcome variables will also be considered.

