Our intervention, a patterned feeding experience (PFE), is not currently used in most neonatal settings. The intervention is based on principles of neural plasticity and neuroprotection and is designed to take advantage of neuronal synaptic development and both experience-expectant and experience-dependent characteristics of the developing brain [13]. In addition, the intervention takes advantage of a regularly occurring caregiving and life-sustaining event in the life of an infant–feeding. The PFE intervention involves a continuity of tactile experiences associated with feeding to train and build neuronal networks supportive of the normal experience. There are virtually no accepted and no tested caregiver behaviors related to enteral feedings in preterm infants, although some recent research has produced evidence for a positive effect of greater caregiver sensitivity to the infant during feeding [14]. Theoretically, our intervention provided at a critical time in neurologic system development and associated with a recurring event such as feeding should enhance neural connections that may be important for later development, particularly language and other cognitive and neurobehavioral organization skills [15].

The overall objective of this study is to test the effect of a PFE from birth to NICU discharge for infants born at 32 weeks gestation and younger. The primary aim of the study is to test the effect of a PFE on neurobehavioral organization at 3 time points: the transition to oral feedings, NICU discharge, and 2 months corrected age (48 weeks PMA). Secondary aims are to test the effect of a PFE on 1) cognitive function at 6 months corrected age; 2) neurobehavioral development; and 3) clinical outcomes including time to first oral feeding, time to full oral feeding, and time to discharge. An exploratory aim is to describe the potential effects of perinatal and infant risk factors including immunologic and genetics influences on the outcome variables (neurobehavioral organization, cognitive function, neurobehavioral development, and clinical outcomes). We hypothesize that infants who receive the PFE will have improved neurobehavioral organization, cognitive function, neurobehavioral development, and clinical outcomes compared to infants who receive usual feeding care in the NICU.

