#### Power analysis

The proposed sample size for the study is based on associations between measures of feeding experience and components of neurobehavioral development and neurobehavioral organization discovered in our previous studies [18–21]. We anticipate 20 % attrition, primarily for medical conditions that arise or are diagnosed after enrollment. The sample size was determined by assuming each aim will be tested using 2-sided tests at *P* = 0.05. For the primary aim, we expect to detect an effect size of at least 0.7 standard deviation (SD) between groups on the final neurobehavioral score, with at least 90 % power using a 2-group *t*-test. However, a random effects model that takes into account the repeated measurements over time is proposed for the analyses of neurobehavior. Differences of the same effect size should improve the power to at least 95 % because of the additional number of observations. Although we have powered the study to test the primary aim, we also considered power for the additional aims. For secondary aim 1 involving a test of the effect of the intervention on cognitive function at 6 months, the same sample size analysis indicates a 2-unit difference (SD = 3) on cognitive development will be detected with 89 % power with only a 2-group *t*-test; the analysis of covariance (ANCOVA) should have more power. For secondary aim 2, the analyses and the sample size calculations are the same as with the primary aim. Secondary aim 3 will be tested in a manner similar to secondary aim 1 and so the sample size calculations should be similar. For the exploratory aim a sample of 96 infants in a test for zero correlation will provide at least 90 % power to detect *r* ≥ 0.26 and at least 80 % power to detect *r* ≥ 0.21.

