### Intervention

The study intervention has two phases using a tactile experience designed to pattern the neurologic system’s theoretical expectation for feeding experience. Phase 1, a period of “attended gavage,” begins within 24 hours of the first gavage feeding, which is generally provided before 72 hours of life. Attended gavage includes tactile containment during the entire gavage infusion by gravity plus 5 minutes. For infants too ill to be removed from the incubator, tactile containment consists of gentle hand containment (placing one hand lightly over the shoulder area and one hand lightly over the lower extremities). If medically stable, the infant is swaddled and removed from the incubator and held. Infants are also offered nonnutritive sucking (NNS) as part of every attended gavage feeding based on prior research showing that NNS facilitates behavioral organization. Instructions related to the tactile containment, swaddling/holding during gavage, and use of NNS are provided for all nursing staff and parents of infants in the intervention group. Gavage feedings are most often provided on a schedule of every 3 hours. Infants on continuous feedings, which may be needed for some infants primarily because of gastric reflux, receive the attended protocol every 3 hours for 15 minutes. Phase 1 of the intervention has varying duration, lasting as long as 12 weeks for infants born at 23 weeks PMA. Attended gavage is a change in practice for most NICUs so we use a team of well-trained study nurses who provide the attended gavage feedings for a minimum of 50 % of the feedings daily. Nursing staff or parents may provide additional attended gavage feedings. We record the occurrence of each attended feeding including who provided the intervention (parent, nursing staff member, or study nurse) and include that “dose” as a covariate in our analyses.

Phase 2 begins when infants in the intervention group begin oral feedings. When an oral feeding is attempted, the infant is held outside the incubator in a swaddled, flexed position either upright or side-lying. We record the volume of feeding prescribed and the amount consumed at each feeding. Infants who are unable to complete the prescribed volume orally or unable to orally feed receive attended gavage as described in Phase 1.

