### Data management and analysis

A relational database has been created. Monthly assessment of data entry processes and a quarterly audit of random samples for completeness are conducted. During the electronic data acquisition process, all sampled data from each of the physiologic channels are stored in a single file. To prepare these data for analysis, the data are digitally filtered to remove frequencies not part of the physiologic signal spectrum. The filtered signal is then applied to our algorithms resulting in the relevant parameters.

Descriptive statistics will be computed for all demographic data to describe the sample and check for missing and outlying data. Descriptive statistics will also be computed for all component measures of study variables. Transformations of non-normally distributed variables will be used for analyses as indicated. Because measures are repeated on the same infant, all analyses will take into account the dependency between measures. Because some infants may be unable to complete the study due to unexpected illness, there will be an “all-infants” dataset (all eligible) and a “per-protocol” dataset (all completers). An intent-to-treat analysis will be performed on the all-infants dataset using all measures obtained. An analysis on the “per-protocol” dataset will be performed using the data from the infants who completed the entire study. All results will be reported as described by the CONSORT guidelines [17]. Analyses will be performed using SAS (SAS Institute Inc., Cary, NC, USA) at an overall alpha = 0.05 significance level.

The primary aim states that infants who receive the PFE will have improved neurobehavioral organization at transition to oral feedings, NICU discharge, and 2 months corrected age (48 weeks PMA). The difference between the PFE and usual care groups on the NAPI will be tested using a repeated-measures ANCOVA. A mixed-model will account for the correlation between the measurements at each time point and allow for differential patterns of missing values at the three time points. A significant difference across these time points will be followed by separate comparisons at each time point; each will be performed at the *P* = 0.05 level of significance.

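### Excluding randomised infants who have not transitioned to oral feeding by 40 weeks PMA stops their outcome collection on an event the intervention is meant to change, which conflicts with the intent-to-treat analysis

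*Protocol article*

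**What the plan says.** All references are to the protocol article.

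- **Randomisation and start of treatment.** The abstract's Methods paragraph says "Infants are enrolled within the first week of life and randomized to an experimental group". Under Intervention, attended gavage "begins within 24 hours of the first gavage feeding, which is generally provided before 72 hours of life".
- **The exclusion.** Under Sample: "Infants who are medically unable to transition to oral feeding by 40 weeks PMA are excluded from further study".
- **Outcomes.** Background lists, as a secondary aim, "clinical outcomes including time to first oral feeding, time to full oral feeding, and time to discharge", and hypothesises that PFE improves these. The primary outcome is the NAPI at the transition to oral feeding, at NICU discharge and at 48 weeks PMA. The BSID III follows at 6 months corrected age.
- **Analysis sets.** Data management and analysis describes an all-infants set, glossed as all eligible infants, and a set of completers. "An intent-to-treat analysis will be performed on the all-infants dataset using all measures obtained". The second analysis is done "using the data from the infants who completed the entire study".
- **Attrition.** Power analysis allows 20%, "primarily for medical conditions that arise or are diagnosed after enrollment".

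**The concern.** The rule acts after randomisation and, in the PFE arm, after weeks of treatment. It depends on whether the infant reaches oral feeding, which the intervention is designed to help. If PFE changes how many infants transition by 40 weeks, or which ones, the infants left at discharge, 2 months and 6 months are no longer the groups that were randomised.

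The analysis cannot repair this. The mixed model tolerates missing values at some of the three NAPI time points, but an infant with none of them contributes nothing to the comparison. The data are lost because the plan stops collecting them, so a later analysis plan could not recover them.

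Group assignment is known to parents, NICU staff and study nurses (Randomization to groups), so the judgement that an infant is medically unable to transition could also differ between arms.

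**Working it through.** **1. Which measures survive the exclusion.**

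| Measure | Planned time | Excluded infant |
|---|---|---|
| NAPI, baseline | at enrolment | available |
| NAPI, transition | transition to oral feeding | none if oral feeding never starts |
| NAPI, discharge | NICU discharge | not collected if discharge follows the exclusion |
| NAPI, 48 weeks PMA | 8 weeks after the 40-week limit | not collected |
| BSID III | 6 months corrected age | not collected |
| Time to full oral feeding; length of stay | counted from the start of oral feeding (Clinical outcomes) | undefined if oral feeding never starts |

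An infant who never starts oral feeding therefore brings only a baseline NAPI to the intent-to-treat analysis.

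**2. The plan's own power figure reproduces.** Inputs from Sample and Power analysis: 120 infants, 20% attrition, 0.7 SD, two-sided 0.05. 120 × 0.80 = 96, or 48 per arm. The noncentrality is 0.7 × √(48/2) = 3.43, and the exact two-group t-test power is 92.4%, consistent with the stated minimum of 90%. The sample size is not at fault. The problem is comparability.

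**3. Illustration of the bias.** The document gives no rate for this exclusion, so the rates and correlations here are assumptions. Suppose each arm loses its lowest fraction p on a latent, normally distributed feeding readiness that has correlation ρ with a standardised outcome, and PFE has no true effect on that outcome. The mean outcome among those kept is ρ × λ(p), with λ(p) = φ(z_p)/(1 − p).

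- λ(0.05) = 0.1031/0.95 = 0.1086
- λ(0.10) = 0.1755/0.90 = 0.1950
- λ(0.20) = 0.2800/0.80 = 0.3500

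Bias in PFE minus control = ρ × [λ(p_PFE) − λ(p_control)].

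| Excluded, control vs PFE | λ difference | ρ = 0.3 | ρ = 0.7 | Type I error, ρ = 0.3 to 0.7 |
|---|---|---|---|---|
| 5% vs 5% | 0 | 0 | 0 | 5.0% |
| 10% vs 5% | −0.0864 | −0.026 SD | −0.061 SD | 5.2% to 6.3% |
| 20% vs 5% | −0.2414 | −0.072 SD | −0.169 SD | 6.6% to 15.5% |

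The type I error uses 60 × (1 − p) infants per arm and the reduced variance after truncation. Exchanging the two rates reverses the sign.

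**4. What that means for power.** Subtract the bias from 0.7 SD and keep 48 per arm with the exact t-test. For 10% vs 5% the detectable difference falls to 0.674 to 0.639 SD and power to about 90% to 87%. For 20% vs 5% it falls to 0.628 to 0.531 SD and power to about 86% to 73%. The planned mixed model, for which the article expects at least 95%, would start from a higher level.

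**The case against.** **The rule concerns medical inability.** Some exclusions will be for illness that has nothing to do with PFE, and the attrition allowance appears to anticipate them. This stands. Treating every excluded infant as the lowest tail of feeding readiness overstates the link to outcome, so the illustration is not an estimate. But the allowance protects numbers, not the comparability of the arms.

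**The rates are invented.** Also true. Losing 20% of controls to this rule alone would use that arm's whole allowance for all causes. Exclusions may be few, or balanced with the same selection, and then this bias is small or zero.

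**Transition may mean completing it.** Usual care speaks of a transition period. On that reading, some excluded infants may have a transition NAPI, which the intent-to-treat analysis keeps. Their 48-week NAPI and BSID III are still lost.

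**Stronger readings that the article does not support.**

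- A reader might infer from the gloss on the all-infants set that excluded infants are removed from it by definition. The set is introduced because some infants may not complete the study, and it is contrasted with completers. The wording is ambiguous, no more.
- A reader might infer that harm from PFE would be concealed. Reporting follows CONSORT and an independent board reviews trial conduct, so unequal exclusions should be visible. That still does not supply the missing outcomes.
- A reader might also fault the completer set for ignoring the 50% minimum dose. That dose applies to the intervention arm only, so selecting on it would filter one arm. It is a separate matter and no part of this point.

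**Conclusion.** The point holds. The exclusion under Sample comes after randomisation, depends on an event that PFE is designed to influence, and stops collection of the 48-week NAPI, the BSID III and any later discharge NAPI. That conflicts with the intent-to-treat analysis, whose set can name these infants but has no later outcomes from them.

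The size cannot be determined from the article. The figures of 0.03 to 0.06 SD (10% vs 5%) and 0.07 to 0.17 SD (20% vs 5%) rest on assumed rates, assumed correlations of 0.3 to 0.7 and selection of the least ready infants. The direction depends on PFE's effect on oral feeding: against PFE if it speeds the transition, in its favour if it delays it. A claim that the result is biased by a known amount, or in a known direction, goes further than the document allows.

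The change should be made while recruitment is open, as Trial status says it is, because outcomes not collected cannot be recovered later.

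**What to change.** 1. Limit the 40-week rule to the feeding observations that cannot be made, and continue outcome follow-up of every randomised infant: discharge NAPI at the bedside, 48-week NAPI and 6-month BSID III in the existing follow-up clinic.
2. Define the all-infants set as all randomised infants by assigned arm, apart from the stated rule on twins who share a card.
3. Report the number and reasons for non-transition by 40 weeks PMA, by arm.
4. State how infants who do not transition enter the clinical outcomes. The durations under Clinical outcomes start at the first oral feeding, so an infant who never starts has no time zero. Simple censoring does not solve this, and the planned ANCOVA does not accommodate censoring.

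The cost is a protocol amendment and a small number of additional assessments. The article already places post-discharge data collection for all enrolled infants in the follow-up clinic (Setting), and the NAPI can be done in an incubator or on oxygen (Neurobehavioral organization). The change affects data collection and analysis sets only, not clinical feeding management.

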#### Power analysis

The proposed sample size for the study is based on associations between measures of feeding experience and components of neurobehavioral development and neurobehavioral organization discovered in our previous studies [18–21]. We anticipate 20 % attrition, primarily for medical conditions that arise or are diagnosed after enrollment. The sample size was determined by assuming each aim will be tested using 2-sided tests at *P* = 0.05. For the primary aim, we expect to detect an effect size of at least 0.7 standard deviation (SD) between groups on the final neurobehavioral score, with at least 90 % power using a 2-group *t*-test. However, a random effects model that takes into account the repeated measurements over time is proposed for the analyses of neurobehavior. Differences of the same effect size should improve the power to at least 95 % because of the additional number of observations. Although we have powered the study to test the primary aim, we also considered power for the additional aims. For secondary aim 1 involving a test of the effect of the intervention on cognitive function at 6 months, the same sample size analysis indicates a 2-unit difference (SD = 3) on cognitive development will be detected with 89 % power with only a 2-group *t*-test; the analysis of covariance (ANCOVA) should have more power. For secondary aim 2, the analyses and the sample size calculations are the same as with the primary aim. Secondary aim 3 will be tested in a manner similar to secondary aim 1 and so the sample size calculations should be similar. For the exploratory aim a sample of 96 infants in a test for zero correlation will provide at least 90 % power to detect *r* ≥ 0.26 and at least 80 % power to detect *r* ≥ 0.21.

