The secondary aims require similar comparisons between study groups on secondary outcomes (cognitive functioning, neurobehavioral development, and clinical outcomes). To test secondary aim 1, differences between the 2 groups on the cognitive outcome measure (BSIDIII cognitive subtest scaled score) at 6 months corrected age will be tested using an ANCOVA with morbidity (NMI) and birth gestation used as covariates. To test secondary aim 2, 4 analyses will be performed, one for each of the feeding-related neurobehavioral outcomes (sucking organization, 2 measures of feeding performance, and HRV). The modeling will be done as above with a repeated-measures mixed-model approach with covariates (birth gestation, morbidity). To test secondary aim 3, separate ANCOVA analyses of the clinical outcomes (time to full oral feeding and length of stay) will be used to compare the 2 groups with the birth gestation age and morbidity covariates.

The intent of the exploratory aim is to identify risk factors of poor neurobehavioral development and cognitive dysfunction in preterm infants. We will test the assumed comparability of randomly assigned groups prior to undertaking further analyses. Secondary analyses will focus on the interactions between risk factors and the intervention differences by first screening the risk factors for effects at *P* = 0.2 and then developing a single exploratory model that includes all of the risk factors that significantly influence the outcome differences between the groups. Additional analyses will focus on the findings for neurobehavioral development including sucking organization and feeding performance, HRV, and clinical outcomes, first by examining the relationships between the risk factors and the components of neurobehavioral development and then by assessing the relationships among the components of neurobehavioral development and the primary outcome measure, the NAPI score (neurobehavioral outcome). The final goal is to identify a model of risk factors, modifiers (measures of neurobehavioral development), and mediators (intervention) that have an effect on the differences between groups.

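### The power stated for the exploratory aim is wrong: with 96 infants and a two-sided 0.05 test, r = 0.26 has about 73% power (stated: at least 90%) and r = 0.21 about 54% (stated: at least 80%)

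*Protocol article*

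**What the plan says.** All the inputs are in the protocol article.

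- **Level and sidedness** (Power analysis): "The sample size was determined by assuming each aim will be tested using 2-sided tests at *P* = 0.05".
- **Sample size** (Sample; Power analysis): "One hundred and twenty preterm infants (60/group) will be enrolled", and "We anticipate 20 % attrition". That leaves 120 × 0.80 = 96, the number used for the exploratory aim.
- **Power claim** (Power analysis): the sentence begins "For the exploratory aim a sample of 96 infants in a test for zero correlation will provide at least". The two minimum powers that it goes on to claim are 90% for correlations of 0.26 and above, and 80% for correlations of 0.21 and above.

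The Data management and analysis section repeats an overall alpha of 0.05. It mentions a different level once. For interactions between risk factors and the intervention, it plans to build a model "by first screening the risk factors for effects at" P = 0.2. The power section does not refer to that threshold.

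**The concern.** A correlation of 0.21 is small for a sample of 96. Its approximate standard error on the Fisher scale is 1/√93 = 0.104, so the true value lies only about two standard errors from zero. At a two-sided 0.05 level that gives power a little above one half, not 80%.

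This is the only power statement for the exploratory aim, which covers perinatal, immunologic and genetic risk factors. A reader who relies on it would expect a true correlation of 0.21 to be missed at most 20% of the time, and one of 0.26 at most 10%. If the claim is wrong, null results for these markers will look more informative than they are.

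**Working it through.** **Inputs.** n = 96; two-sided α = 0.05; r = 0.26 (stated power at least 90%) and r = 0.21 (at least 80%). All are from the Power analysis section.

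**Formula.** Fisher z test of zero correlation: power = Φ(atanh(r)·√(n − 3) − z₁₋α/₂). The opposite tail is negligible. Here √93 = 9.6437 and z = 1.960.

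**Attempt to reproduce the stated figures**
- r = 0.26: atanh = 0.26611; 0.26611 × 9.6437 = 2.566; 2.566 − 1.960 = 0.606; Φ = **72.8%**.
- r = 0.21: atanh = 0.21317; 0.21317 × 9.6437 = 2.056; 2.056 − 1.960 = 0.096; Φ = **53.8%**.

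Two other methods agree. Simulating the t test of a Pearson correlation (200,000 bivariate normal samples) gives 73.2% and 53.9%. A noncentral t calculation with a fixed regressor gives 74.3% and 54.9%. The shortfalls of about 17 and 26 percentage points are too large to come from rounding or choice of formula.

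**Other readings (Fisher z)**

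| Reading | r = 0.26 | r = 0.21 |
|---|---|---|
| Stated in the protocol | at least 90% | at least 80% |
| n = 96, two-sided 0.05 | 72.8% | 53.8% |
| n = 96, one-sided 0.05 | 82.2% | 65.9% |
| n = 120, two-sided 0.05 | 82.1% | 63.5% |
| n = 120, one-sided 0.05 | 89.1% | 74.6% |
| n = 96, two-sided 0.20 | 90.1% | 78.1% |

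No reading at 0.05 delivers both claims. Taking the printed values as R² instead of r gives over 99% for both, so that is not the explanation either.

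**Detectable correlation at n = 96, two-sided 0.05:** r = tanh((1.960 + z_power)/√93).
- 80%: (1.960 + 0.842)/9.6437 = 0.2905, so r = **0.283**.
- 90%: (1.960 + 1.282)/9.6437 = 0.3361, so r = **0.324**.

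**Sample size the stated claims need:** n = ((1.960 + z_power)/atanh(r))² + 3, rounded up.
- r = 0.26, 90%: (3.2415/0.26611)² + 3 = 151.4, so **152**.
- r = 0.21, 80%: (2.8016/0.21317)² + 3 = 175.7, so **176**.

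Both exceed the 120 to be enrolled.

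**Check on the rest of the paragraph.** With 48 per group and a two-sided 0.05 t test, 0.7 SD gives 92.4% (stated: at least 90%). A 2-unit difference with SD 3 gives 89.8% (stated: 89%). So 96 analysed infants and two-sided 0.05 are the paragraph's working assumptions, and only the exploratory sentence departs from them.

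**The case against.** The arithmetic is not open to dispute, and an unseen analysis plan cannot explain it, because the article itself prints n, level, r and power. The case on the other side concerns weight and cause.

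1. *It is only the exploratory aim.* The protocol says the study was powered for the primary aim and that power for the others was merely considered. No sample size, primary test or secondary test rests on this sentence. This stands, and it limits the consequences.

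2. *The harm is inferred.* The document never says that a null result will be taken to rule out a correlation. The exploratory aim is described as descriptive and model-building. Where the 0.2 screen applies, a marker is not dropped at 0.05, so the miss rates at 0.05 are not those of the screen. This also stands. However, the protocol ties that screen to interactions with the intervention, and its overall 0.05 level could still govern simple correlations.

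3. *The level may have been omitted, with the calculation otherwise sound.* At two-sided 0.20 the detectable correlations with 96 infants are 0.260 (90%) and 0.217 (80%), close to the printed values. This is a plausible origin, but the document does not say so. It would contradict the level stated for every aim, and r = 0.21 would still fall short of 80%, at 78.1%. It does not rescue the sentence as written.

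**Conclusion.** The concern holds. With the protocol's own sample size, level and sidedness, power is about 73% for r = 0.26 and about 54% for r = 0.21. A true correlation of those sizes would be missed about 27% and 46% of the time, against the implied maxima of 10% and 20%.

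The calculation assumes a simple Pearson correlation between roughly normal variables, 96 independent infants with both measurements, and one test at two-sided 0.05 with no allowance for multiple markers. That the printed figures came from a 0.20 level is a conjecture, and the conclusion does not depend on it.

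The effect is confined to the exploratory aim. The t-test power for the primary aim and for secondary aim 1 reproduces.

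**What to change.** Replace the exploratory sentence in Power analysis with, for example: *With 96 infants and a two-sided test of zero correlation at 0.05, there is about 80% power to detect r = 0.28 and about 90% power to detect r = 0.32.* The unrounded values are 0.283 and 0.324, so the two-decimal figures give marginally less (79.2% and 89.2% by Fisher z). If the at-least wording is kept, use 0.29 (82.1%) and 0.33 (91.1%).

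If the authors did mean a 0.20 level, they should say so in that sentence and give about 90% for r = 0.26 and about 78% for r = 0.21. This is the weaker option. The 0.2 screen is described for interactions between risk factors and the intervention, and the power of a simple correlation test does not carry over to that test.

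The cost is one sentence and a less favourable figure. Enrolment, design and the primary analysis do not change.
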